## Abstract

**Background:**

Men who have sex with men (MSM) in India are a key group at risk for HIV acquisition and transmission. They are also an extremely marginalized and stigmatized population, facing immense psychosocial stressors including, but not limited to, stigma, homophobia, discrimination, criminalization, low self-esteem, low self-acceptance, distress, and, as a result, high rates of mental health problems. Although these multi-level psychosocial problems may put MSM at high risk for HIV acquisition and transmission, currently HIV prevention interventions in India do not address them. This paper describes the design of a psychosocial intervention to reduce HIV risk for MSM in India.

**Methods:**

Funded by the National Institute of Mental Health, this study is a two-arm randomized clinical efficacy trial of a self-acceptance based psychosocial HIV prevention intervention, informed by the minority stress model and syndemic theory, that was developed with extensive community-based formative work and input from the Indian MSM community and key informants who are knowledgeable about the experiences faced by MSM in India. Participants are MSM in Chennai and Mumbai who endorsed recent sexual behaviors placing them at high risk for HIV/sexually transmitted infection (STI) acquisition and transmission. Enrolled participants are equally randomized to either 1) the experimental condition, which consists of four group and six individual counseling sessions and includes standard of care HIV/STI testing and counseling, or 2) the standard of care condition, which includes HIV/STI testing and counseling alone. The primary outcomes are changes in the frequency of condomless anal sex acts and STI incidence (syphilis seropositivity and urethral, rectal, and pharyngeal gonorrhea and chlamydia infection. Major study assessment visits occur at baseline, 4-, 8-, and 12-months.

**Discussion:**

HIV prevention interventions that address the psychosocial stressors faced by MSM in India are needed; this study will examine the efficacy of such an intervention. If the intervention is successful, it may be able to reduce the national HIV/AIDS burden in India while empowering a marginalized and highly stigmatized group.

**Trial registration:**

ClinicalTrials.gov Identifier: NCT02556294, registered 22 September 2015.

## Background

India is home to an estimated 2.1 million people living with human immunodeficiency virus (HIV), nearly 6% of all people living with HIV in the world [1]. With 4.3% of men who have sex with men (MSM) in India living with HIV, UNAIDS has identified this population as a key group at risk for HIV acquisition and transmission [1, 2]. MSM in India may also be a ‘bridge’ population, spreading HIV to other populations, since many MSM marry and engage in unprotected intercourse with their wives, while still partaking in risky sexual behavior with men [3, 4].

MSM in India are extremely marginalized and stigmatized, and face many sources of psychosocial stress including stigma, homophobia, discrimination, and even criminalization [5]. While MSM sexual activity is prevalent in the country, such sexual behavior is taboo [3, 6] and illegal [7], influencing the MSM community to be largely secretive and silent, and placing them at risk of abuse. Prior work in India has found high levels of perceived stigma, harassment from police and “thugs,” and negative interactions with healthcare providers among MSM, and suggests that Indian MSM face a variety of psychosocial problems including low self-esteem, internalized homophobia, difficulty in coming out to others, family pressure to marry and have children, leading a “double life” (being in a relationship with a woman, despite having a same-sex sexual orientation), difficulty disclosing one’s MSM status to one’s female partner or spouse, relationship problems with male sexual partners, and, for those who are HIV-positive, disclosing and coping with one’s HIV status [8]. Furthermore, due to such multi-level psychosocial stressors, this population may also experience high rates of psychiatric disorders; a mental health study in Mumbai, India identified major depressive episodes (29%), anxiety disorders (24%), and suicidal ideation (45%) among MSM, each of which were independently associated with sexual risk behavior that places men at greater risk of acquiring HIV [9, 10]. Among MSM in the United States (US) [11–13] and other regions of the world [14, 15] it has been shown that co-occurring “syndemics” of psychosocial health problems accelerate HIV acquisition among MSM. Due to the extremely stigmatizing cultural context and subsequent high rates of mental health problems, MSM in India may experience even more psychosocial distress than MSM in other regions of the world, which may further potentiate HIV spread in this group [10, 16].

Despite the high psychosocial stress, current HIV prevention interventions for MSM in India are primarily focused on condom distribution and HIV education, but do not address the many psychosocial problems that impact this population and may increase HIV risk. Yet, internationally, HIV prevention interventions in MSM that are based on theoretical models, span multiple sessions, and include interpersonal skills training and multiple delivery methods have been shown to be effective [17, 18]. Thus, with extensive community-based formative work and input from the Indian MSM community and their providers [8, 10, 16, 19–29], we designed a psychosocial intervention to increase self-acceptance and reduce HIV acquisition and transmission risk among MSM in India.

### Study objectives

The primary aim of this study is to examine the efficacy of the psychosocial intervention with standard of care (standard HIV/sexually transmitted disease (STI) counseling and testing) in comparison to just the standard of care on [1] changes in frequency of condomless anal sex acts, and [2] STI incidence. Secondary aims are [1] to examine the efficacy of the psychosocial intervention on potential mediators, such as self-acceptance, self-esteem, and distress, and (b) to assess the incremental cost-effectiveness of the psychosocial intervention relative to standard of care.

## Methods/design

### Study design

The study is a two-arm randomized clinical trial of a self-acceptance based psychosocial HIV prevention intervention designed for MSM in Chennai and Mumbai, India. Approximately 608 participants are randomized to either the psychosocial intervention (with standard of care) condition or solely to the standard of care (control) condition. Participants in both arms complete assessments at four timepoints: baseline (psychosocial assessments and HIV/STI testing), post-intervention (psychosocial assessments only), 8-month follow-up (psychosocial assessments only), and 12-month follow-up (psychosocial assessments and HIV/STI testing). The study flow is demonstrated in Fig. 1.

**Fig. 1 Fig1:**
[figure not shown]
Flow chart of study intervention process

### Participants

#### Eligibility criteria

Participants are MSM living both with and without HIV in Chennai and Mumbai, India. To be eligible for the study, participants must be: (a) aged 18 or older; (b) a man who has sex with men; (c) a Kothi or Double Decker MSM subtype; (d) fluent in English, Tamil, or Hindi; and (e) at risk for acquisition of HIV (defined by any of the following in the four months prior to screening: protected or unprotected anal sex with four or more male partners, a diagnosis of a STI, a history of transactional sex activity, or condomless anal sex with a man who was HIV unknown status or serodiscordant). Participants are excluded if they are under 18 years old; are unable or unwilling to provide informed consent; have an active, untreated, unstable major mental illness (i.e., untreated psychosis or mania) that would interfere with treatment or any primary psychotic disorder, even if treated; or are deemed by the local PI or study outreach staff to be inappropriate for participation in the study (e.g., engaging in deception about eligibility).

Instead of being categorized under one identity (e.g. “gay”), MSM in India tend to be categorized by behavior and sex role. Subgroups include *Kothi* (feminine acting/appearing, predominately receptive partners in anal sex), *Panthi* (masculine appearing, predominately insertive partners in anal sex), and *Double Deckers* (both insertive and receptive in anal sex) [3, 30, 31]. Based on input from the Indian community members and colleagues, Kothi and Double Decker MSM were deemed most likely to benefit from the intervention, as they tend to be the most stigmatized and harassed. Prior research suggests that they would prefer not to have an intervention with Panthi MSM or other MSM identities; thus, the study is only open to Kothi and Double Decker MSM.

#### Sample recruitment procedures

In both cities, recruitment efforts are led by non-governmental organizations (NGOs) with extensive experience working with and recruiting MSM. These NGOs already follow thousands of MSM in programs not associated with the study, and have previously mapped out where MSM meet, including “cruising” sites. The NGOs recruit participants for this study via word-of-mouth and extension of current outreach efforts. All recruiters are aware of local opinions regarding sexuality, and recruit discreetly.

#### Randomization

Approximately half of participants are randomized to the psychosocial intervention condition (*N* = ~ 300 across both sites; ~ 150 per study site) and approximately half are randomized to the standard of care control condition (*N* = ~ 300 across both sites; ~ 150 per study site). Random assignments are generated by an interactive web-based response system that can be monitored across study sites. Those randomized to the psychosocial intervention are assigned in order of their randomization into batches of 8 participants for the purpose of doing group intervention sessions together. All batches, except potentially the final batch, are expected to have 8 participants.

### Procedure

#### Psychosocial intervention

The psychosocial intervention focuses on self-acceptance/self-esteem as a central protective resilience factor fostering HIV-related self-care and decreasing mental-health related distress for MSM in India [21]. Informed by community work spanning a decade [22], the intervention acknowledges many psychosocial problems for MSM in India across many levels, including community, family, and individual; but those who appear to be most resilient also have high self-acceptance. The intervention additionally places topics within the unique context of Indian MSM. We hypothesize that emphasizing self-acceptance in an HIV prevention intervention will increase self-care and decrease distress among MSM in this setting. Participants randomized to the psychosocial intervention receive four group counseling sessions and six individual counseling sessions that are conducted in either Hindi or Tamil, in addition to the standard of care (see below).

Each group session lasts approximately two hours and focuses on fostering self-acceptance in participants through developing skills, knowledge, and confidence in their own ability to overcome obstacles in their lives. Sessions begin with participants sharing one proud moment that occurred in the previous week, and feature a variety of interactive activities, including discussions, videos, games, and role-plays. The themes of the group sessions are: [1] self-acceptance: barriers and strategies, and coping with pressures from family and society; [2] safety and self-care: safer ways to meet men, and alcohol and substance use and misuse; [3] health risk: HIV education and STI vulnerability; and [4] tying it all together: risk reduction skills and looking to the future.

The purpose of individual sessions is to provide additional support for participants struggling with issues such as disclosure of their MSM or HIV status, case management, or linkage to additional care. Each session lasts approximately one hour, and participants are free to discuss topics that they are not comfortable addressing in front of a group. The themes of the individual sessions are: [1] self-esteem and coming out experience; [2] risk limits; [3–5] risk education, risk reduction, and problem solving; and [6] relapse prevention and wrap up/exit interview.

#### Standard of care

Participants in both conditions receive the standard of care HIV/STI testing and counseling at their baseline and 12-month follow-up assessments. HIV/STI testing occurs in a lab associated with the study site. Specifically, participants are tested for HIV, syphilis, chlamydia, and gonorrhea.

In addition to the HIV/STI testing, participants also receive a pre-test and post-test HIV counseling session, as is standard practice in India. At counseling sessions, risky behaviors, self-perception of risk, barriers to changing the risky behaviors, and support plans in the case of an HIV-positive result are discussed. Participants are also given educational materials on topics such as Hepatitis B, C, and D, HIV infection, STIs, overdose prevention/ first aid at overdose, drug use harm reduction, safe sex, and contraception.

#### Study assessments.

The study is comprised of four main assessments: baseline, 4-month follow-up, 8-month follow-up, and 12-month follow-up. All assessments contain self-report questionnaires, filled out with the help of a blinded independent interviewer on a tablet. To minimize the social desirability bias that may occur when an interviewer is present, each major assessment visit also includes an audio computer assistant self-interview (ACASI) component without an interviewer present to measure sensitive sexual behavioral data. HIV/STI testing also occurs at the baseline and 12-month follow-up assessments.

##### Primary outcomes

[1] Changes in condomless anal sex measured with self-report using ACASI from baseline to 4-, 8-, and 12-month follow-up assessments. Based on a previous study [32, 33], participants are asked to estimate their number of sexual partners by HIV status, sex, and number of times having anal intercourse with and without a condom in the past 4 months. [2] STI incidence, measured through HIV/STI testing at baseline and the 12-month follow-up assessment. To test for HIV and syphilis, the participant has a small amount of blood drawn. HIV screening is done by rapid card tests using serum or plasma, and syphilis screening is done using serum by the Rapid Plasma Reagin (RPR) assay or the venereal disease research laboratory (VDLR) test. Additionally for syphilis, nonspecific and positive tests (RPR) are confirmed by specific tests (Microhemagglutination Assay for Treponema pallidum Antibodies (MHA-TP) or fluorescent treponemal antibody absorption (FTA-ABS)) and titers of prior tests and treatment histories are obtained in order to ensure that positive results indicate incident infections. To test for chlamydia and gonorrhea, participants provide a small urine sample for testing by nucleic acid amplification testing (NAAT), and a lab employee takes an oropharyngeal sample and a rectal swab using standard assays. All positive cases of STIs are treated on site, and anyone who tests positive for HIV is referred for outside treatment where treatment is provided free of charge.

##### Secondary outcomes

Self-acceptance and self-esteem are assessed by asking the degree to which (scale 1–10) “you accept yourself,” [19, 34] the 10-item Rosenberg scale, which uses a four-point Likert scale and has previously been used in India [35, 36], and the Collective Self-Esteem Scale (CSES), a 16-item measure that assesses thoughts and feelings associated with one’s social group on a 7-point Likert scale [37]. Distress is assessed through the Center for Epidemiological Studies Depression Scale (CES-D) [38], which has been used in India, along with the Primary Care Post Traumatic Stress Disorder Screen. Culturally-relevant sexual minority stress questions, such as the frequency and experiences of harassment, violence, losing jobs and friends, and family and social discrimination in both childhood and adulthood are also assessed. For the cost-effectiveness analysis, resource utilization data for the delivery of the intervention is collected, including the time spent by all staff preparing for and on the intervention.

### Data analyses

#### Preliminary analyses

The distribution of all variables will be assessed, including correlations between variables and the primary/secondary outcomes. Patterns of missing data will be assessed, and attrition effects will be evaluated by testing whether systematic difference exist between study completers and non-completers. Key baseline characteristics will be examined between the intervention and control conditions to ensure they are balanced; if they are not, subsequent analyses will assess whether these characteristics are confounders of the intervention.

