#### Primary analyses

In the primary analysis, 1) changes in the frequency of condomless anal sex from baseline to the 4-, 8-, and 12-month follow-ups and 2) incident STIs from baseline to the 12-month follow-ups between the intervention and control conditions will be compared. Generalized linear models with link functions, selected based on the distribution of the dependent variable, will be used to analyze longitudinal data. To account for repeated measures of the outcome [39], the generalized linear models will be estimated using generalized estimating equations with robust standard error estimates. All statistical tests will determine significance with an alpha level of 0.05. To reduce the threat of bias, the intention-to-treat principle will be utilized, where individuals will be analyzed according to the condition to which they were randomized, regardless of their fidelity to the condition.

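### Covariates are considered only after an observed baseline imbalance and an undefined confounder check; a set fixed in advance would use the baseline data better

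*Protocol article*

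**What the plan says.** All places are in the Protocol article.

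- **Preliminary analyses.** "Key baseline characteristics will be examined between the intervention and control conditions to ensure they are balanced"; and then "if they are not, subsequent analyses will assess whether these characteristics are confounders of the intervention". The section lists no characteristics, sets no threshold for imbalance and no criterion for a confounder, and does not say what follows for the primary estimate if one is found.
- **Primary analyses.** Two comparisons are planned: "changes in the frequency of condomless anal sex from baseline to the 4-, 8-, and 12-month follow-ups", and "incident STIs from baseline to the 12-month follow-ups between the intervention and control conditions will be compared". On the model, "the generalized linear models will be estimated using generalized estimating equations with robust standard error estimates". No covariate is named. On significance: "All statistical tests will determine significance with an alpha level of 0.05".
- **Randomization.** Allocation is about 1:1, with roughly "150 per study site" in each arm. "Random assignments are generated by an interactive web-based response system that can be monitored across study sites". Stratification by site is not mentioned.
- **Standard of care; Primary outcomes.** HIV and STI status and the number of condomless acts are all measured at baseline.

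**The concern.** Confounding in the observational sense does not arise at baseline in a properly randomised comparison: any difference between arms is chance, and the standard error already allows for it. What makes a covariate worth including is how strongly it predicts the outcome, and that can be judged before any data are seen. A rule that waits for an imbalance selects on the wrong property. It usually leaves strong predictors out because they happen to be balanced.

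Two things are at stake. The first is precision, since the trial collects baseline values that could sharpen the comparison at no cost. The second is clarity: if a characteristic is found unbalanced and related to the outcome, the article does not tell the analyst which of two estimates is the main one.

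**Working it through.** **1. The plan's own figures.** Power considerations and sample size calculations gives 480 completers for 90% power, then 20% attrition: 480 / (1 − 0.20) = 600, which reproduces the article's figure. The goal of 608 is 76 batches of 8 (76 × 8 = 608). No figure is given for covariate adjustment. The 480 is taken below as the starting point, 240 per arm, with a two-sided 0.05 test assumed because sidedness is not stated.

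**2. How often chance imbalance appears.** The article gives neither the number of characteristics nor a test, so this is illustrative only. With k independent tests at 0.05, the chance of at least one apparent imbalance under sound randomisation is 1 − 0.95^k:

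- k = 5: 23%
- k = 10: 40%
- k = 20: 64%

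This is the chance that the first step fires. It is not the chance that a model changes, because the confounder check comes second.

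**3. Precision available from a fixed covariate.** The correlation rho between covariate and outcome is not in the article; it is assumed over a range. In a linear model, variance relative to an unadjusted follow-up comparison is 1 − rho². Starting from 90% power at 480, power becomes Φ[(1.960 + 1.282)/√(1 − rho²) − 1.960], and the equivalent sample size is 480 × (1 − rho²).

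| rho | variance factor | power | equivalent N |
|---|---|---|---|
| 0.3 | 0.91 | 92.5% | 437 |
| 0.5 | 0.75 | 96.3% | 360 |
| 0.7 | 0.51 | 99.5% | 245 |

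At rho = 0.5, 1/0.75 = 1.33, which is like having one third more participants. That figure stands or falls with the assumed 0.5.

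**4. What the imbalance trigger recovers.** Simulation with 6,000 replicates, n = 480, one normal covariate, effect 0.296 SD (the difference that gives 90% power at 240 per arm). The trigger was an imbalance at p < 0.05 plus a change of more than 10% in the estimate; both thresholds are assumptions.

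| rho | type I error: triggered | type I error: fixed | power: triggered | power: fixed |
|---|---|---|---|---|
| 0.3 | 4.6% | 4.9% | 90.4% | 92.2% |
| 0.5 | 4.1% | 4.8% | 91.1% | 96.4% |
| 0.7 | 3.8% | 5.6% | 91.1% | 99.5% |

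The Monte Carlo standard error near 5% is √(0.05 × 0.95/6000) = 0.28 percentage points, so the fixed model's 5.6% is about two standard errors from nominal.

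With 5 or 10 covariates that together explain an assumed 25% of outcome variance, the result was similar: power about 90% with the trigger against 96% with fixed adjustment, and type I error about 4.4%. If an analyst took the better of the unadjusted and triggered p-values, type I error rose to 5.3% (5 covariates) and 5.7% (10 covariates).

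**5. Condomless acts: baseline is already used.** Steps 3 and 4 start from an unadjusted follow-up value. The acts outcome is a change from baseline, so the relevant comparison is a change score against conditioning on baseline. Relative variances are 2(1 − rho) and 1 − rho². Their ratio is (1 − rho²)/[2(1 − rho)] = (1 + rho)/2:

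- rho = 0.3: 0.65
- rho = 0.5: 0.75
- rho = 0.7: 0.85

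In the same simulation a plain change score had power 78.5%, 89.6% and 98.6%, against 92.2%, 96.4% and 99.5% for conditioning on baseline.

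**6. Incident STI and site.** The article gives no control incidence, no association between baseline and later STI, and no between-site difference. No gain can be computed for either.

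**The case against.** The strongest reply is that the article says later analyses will assess confounding. It does not say that covariates will be added to the primary model or that an adjusted estimate will replace the primary one. An unadjusted primary analysis with a supplementary check fits the text equally well. This stands. A reader might infer that the primary estimate is data-driven, but the document does not state it; it leaves the status of any adjusted result open.

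A reader might also infer that the nominal 0.05 no longer holds. The simulations do not support that: the rule as followed is at or slightly below 5%, and even picking the better of two results adds less than one percentage point.

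A third tempting reading is that baseline risk is simply given up. That is wrong for condomless acts, which are analysed as change from baseline. The variance formulas are also linear-model approximations, whereas the plan is a generalised linear model for repeated counts and a binary outcome. In a logistic model, for example, adjustment changes the conditional odds ratio and does not just shrink its variance.

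Finally, the absence of a site term is not an error: stratification by site is not stated, the per-site numbers are approximate, and a covariate list may be in an analysis plan that is not shown. That answers a charge of omission. It does not fully answer this point, because the imbalance trigger is a stated method and a fixed covariate set would have to override it.

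**Conclusion.** The point holds in a limited form. The article makes consideration of covariates depend on chance imbalance and an undefined confounder check, and leaves the standing of any adjusted result unsaid. The cost is efficiency and clarity, not validity: roughly 91% power against 96% at an assumed rho of 0.5, almost no difference at 0.3 (90.4% against 92.2%), and more at 0.7 (91.1% against 99.5%). For acts, the variance could fall by 15% to 35% relative to a change score over the same range of rho.

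These sizes rest on assumed correlations, assumed trigger thresholds and a linear model, and the article supplies none of them. They show direction and order of magnitude and do not predict this trial's power. The improvement is worth making because it is nearly free, but the plan is not unsound without it.

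**What to change.** Replace the imbalance trigger with covariates named in advance for the two primary models estimated by generalised estimating equations. One workable choice is baseline condomless acts (suitably transformed) and site for the acts outcome, and baseline STI status and site for incident STI. Other prespecified forms are defensible, such as keeping baseline in the repeated-measures response with a common baseline mean across arms. What matters is that the choice is fixed before outcome data by arm are seen.

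Report baseline characteristics by arm descriptively. State that any adjustment prompted by an observed imbalance is a sensitivity analysis and does not replace the primary estimate.

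The cost is a few sentences in the analysis section. Site and the baseline measurements are already recorded, so no new data, visits or participants are needed.
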